### Sample size and power analysis

The target sample size of 500 participants (250 per arm) was calculated based on the primary outcome of change in PTSD symptoms, as measured by the PCL-5. The sample size was determined to detect a minimum effect size (Cohen’s d) of 0.4, which represents a clinically meaningful difference in PTSD symptoms between the two intervention arms. This effect size is consistent with previous studies of psychosocial interventions for conflict-affected populations [46]. The power calculation assumed a two-sided significance level of 0.05, a power of 80%, and an intra cluster correlation coefficient (ICC) of 0.05 to account for the clustering of participants within IDP camps or communities. The ICC was estimated based on previous cluster-randomized trials of mental health interventions in humanitarian settings [47]. To account for potential attrition, the sample size was inflated by 15%, based on an anticipated dropout rate of 10–15% over the 12-week intervention period. This attrition rate is consistent with previous longitudinal studies of IDPs and takes into consideration the potential challenges of retention in the context of ongoing displacement and insecurity [48].

Based on these parameters, a total of 20 clusters (10 per arm) with an average of 25 participants per cluster (500 participants in total) will provide sufficient power to detect a clinically meaningful difference in PTSD symptoms between the in-person and mobile-delivered LSE interventions, while accounting for clustering and attrition.

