### Data analysis

Implementation outcomes will be assessed using the Acceptability of Intervention Measure (AIM), Intervention Appropriateness Measure (IAM), Facilitator Fidelity logs, observation checklist of program implementation and observation of staff training on the life skills curriculum, and Feasibility of Intervention Measure (FIM) [59]. Cost-effectiveness will be calculated by estimating the total program costs and comparing them to the achieved health outcomes.

Qualitative data analysis will employ a reflexive thematic analysis approach using both inductive and deductive coding strategies to identify key themes related to implementation, acceptability, fidelity, and feasibility. Transcripts will be coded iteratively to identify emerging themes and patterns, with constant comparison within and across cases. Memos and matrices will be used to facilitate synthesis and interpretation. Triangulation of qualitative and quantitative findings will be performed to enhance validity and identify convergent and divergent results [60, 61].

Quantitative data analysis will follow an intention-to-treat approach, using mixed-effects linear regression models to assess intervention effects on primary and secondary outcomes. Models will include fixed effects for time, group assignment, and their interaction, and random effects for clusters and participants. Baseline characteristics will be included as covariates to adjust for potential confounding. missing data will be handled using list wise deletion (complete case analysis) or multiple imputation (MI) methods.

Effect sizes will be expressed using Cohen’s (standardized mean differences) with 95% confidence intervals. To account for potential biases from unmeasured confounders, propensity score matching will be employed to adjust the effect size estimates.

intervals. Subgroup analyses will explore differential effects by gender, age, displacement duration, and baseline symptom severity. Sensitivity analyses will be conducted to assess the robustness of the findings to different assumptions and methods.

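### The plan lets missing data be handled by listwise deletion or multiple imputation with no rule for choosing; the listwise option conflicts with its intention-to-treat statement and may discard observed 12-week scores

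*Protocol article*

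**What the plan says.** In the protocol article, Data analysis states that "Quantitative data analysis will follow an intention-to-treat approach". It specifies a mixed-effects linear model with time, group and their interaction, random effects for cluster and participant, and baseline characteristics as covariates (not listed). The same paragraph ends: "missing data will be handled using list wise deletion (complete case analysis) or multiple imputation (MI) methods". It does not say which method is primary, what would trigger one or the other, or whether deletion is by participant or by record. Sensitivity analyses are promised only in general terms, and neither method is given that role.

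Outcomes and measures sets the primary outcome as PCL-5 change from baseline to 12 weeks, with assessments at baseline and at 3, 6 and 12 months. Sample size and power analysis inflates for attrition "based on an anticipated dropout rate of 10–15% over the 12-week intervention period". No loss after week 12 is given.

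**The concern.** Two problems sit in one sentence.

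- **The primary analysis is not fixed.** The two methods imply different analysis sets and can give different estimates. With no rule, the choice could follow the results.
- **One of the two options suits neither the stated principle nor the stated model.** Listwise deletion takes randomised people out of an intention-to-treat analysis. It is also unnecessary, because a likelihood-based mixed model uses every observed visit under missing-at-random. If complete case means complete at all four assessments, a person with a valid 12-week PCL-5 is removed for missing month 6 or month 12. A missing baseline covariate has the same effect.

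At stake are some precision and, more importantly, the credibility of the comparison between in-person and mobile delivery if the people who leave later differ between the arms.

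**Working it through.** **Inputs from Sample size and power analysis.** 500 participants, 250 per arm; "a total of 20 clusters (10 per arm) with an average of 25 participants per cluster"; d = 0.4; two-sided 0.05; 80% power; ICC 0.05; 10–15% dropout to week 12. **Assumption (not in the document):** cumulative loss by month 12, varied from 20% to 50%.

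**1. The plan's own figure.** Individually randomised n per arm = 2 × ((1.960 + 0.842)/0.4)² = 98.1, so 99. Design effect = 1 + (25 − 1) × 0.05 = 2.2. 99 × 2.2 = 217.8, so 218 per arm. For attrition, 218/0.85 gives 257 per arm (514 in total) and 218 × 1.15 gives 251 (502 in total). Both are within 3% of 500, so the sample size is reproduced and is not in dispute.

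**2. Analysis sets.** Multiple imputation keeps all 500. Complete case at week 12 keeps 500 × 0.90 = 450 down to 500 × 0.85 = 425. Complete case over all four assessments keeps fewer.

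**3. Observed primary outcomes discarded if deletion is by participant.** With 15% lost by week 12, 425 have a 12-week score. With 30% lost by month 12, 350 are complete throughout. Discarded: 425 − 350 = 75, or 18% of 425.

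**4. Power.** With m analysed per cluster, effective n per arm = 10m/(1 + (m − 1) × 0.05) and noncentrality = 0.4/√(2/effective n), referred to a noncentral t with 18 df. This assumes equal cluster sizes and takes no credit for baseline adjustment.

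- m = 21.25 (N = 425): design effect 2.0125, effective n 105.6, power 78.5%.
- m = 17.5 (N = 350): design effect 1.825, effective n 95.9, power 74.5%.

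The range, with 15% lost by week 12:

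| Lost by month 12 (assumed) | Complete at all visits | 12-week scores discarded | Power, t (18 df) | Power, normal |
|---|---|---|---|---|
| no deletion of observed scores | – | 0 of 425 | 78.5% | 82.8% |
| 20% | 400 | 25 (6%) | 77.3% | 81.7% |
| 30% | 350 | 75 (18%) | 74.5% | 79.1% |
| 40% | 300 | 125 (29%) | 71.0% | 75.7% |
| 50% | 250 | 175 (41%) | 66.4% | 71.2% |

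**5. Can the choice move the estimate?** An illustrative simulation used 400 runs, a true effect of −0.40 SD, about 15.5% lost by week 12 and 35% by month 12, and dropout depending on the last observed score. All of these are assumptions. The 12-week effect was estimated with baseline adjustment.

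| Dropout mechanism | All observed 12-week scores | All-visit completers only |
|---|---|---|
| same in both arms | −0.41 | −0.38 |
| high scorers leave in one arm, low scorers in the other | −0.40 | −0.62 |

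The second row is a deliberately strong contrast. It shows that a material difference is possible, not how large it will be in this trial.

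**The case against.** The strongest reply is that only the unqualified "missing data will be handled using list wise deletion (complete case analysis) or multiple imputation (MI) methods" is on the page, and that the harms depend on how it is read. Much of this stands.

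- **A reader might infer that the plan will discard observed 12-week scores.** The article does not say so. If only records with a missing outcome are dropped from long-format data, observed 12-week scores survive unless a covariate is missing. Nor does the article say that one model over all four assessments gives the primary result; Table 1 places the 6- and 12-month outcomes under Maintenance.
- **A reader might infer that the whole sentence contradicts intention-to-treat.** Only the listwise option does.
- **A reader might charge the 50–75 early dropouts (10–15% of 500) to listwise deletion.** They have no 12-week score under any method, and the sample size already allows for them.
- **A reader might expect the mixed model to remove bias from early leavers who do worse.** It does not when their poorer change is not predicted by observed data. Suppose dropout is 5% in one arm and 20% in the arm with the better outcome, leavers change 0.5 SD less, and the effect among those who stay is −0.40 (all assumptions). The effect in everyone randomised is then −0.40 + (0.20 − 0.05) × 0.5 = −0.325. A simulation of this case (150 runs) gave −0.394 by complete case and −0.395 by mixed model, so both miss by the same amount.
- **A reader might assume that phone loss or sharing in the mobile arm leads to missing outcomes.** The article has trained research assistants assess outcomes and does not say that the PCL-5 is collected by WhatsApp. Dropout that differs by arm is possible, not shown.

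It can also be said that such detail belongs in an analysis plan that is not shown. That is fair for imputation settings. It does not cover this sentence, which states a rule and puts an unsuitable method on an equal footing with a suitable one.

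**Conclusion.** The point holds in a limited form. What the text itself establishes is that two missing-data methods are permitted, neither is primary, no rule selects between them, and the listwise option conflicts with the intention-to-treat statement in the same paragraph.

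The loss of observed primary outcomes is conditional on deletion by participant across visits or for a missing covariate. Under that reading the loss of power is modest: about 4 percentage points at an assumed 30% loss by month 12, when 75 of 425 scores are dropped. The number actually lost cannot be fixed from the article. Bias is possible if later dropout works differently in the two arms, but no particular size of bias is supported. This should be corrected; it does not call the sample size or the design into question.

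**What to change.** In Data analysis, replace the missing-data sentence, and align any separate analysis plan with it:

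- **Primary:** the likelihood-based mixed model on all observed PCL-5 values for every randomised participant, never deleting a person for a later missed visit, with missing baseline covariates imputed.
- **Listwise deletion:** remove it as a primary option. Keep complete-case analysis, if wanted, only as a labelled sensitivity analysis, stating whether it is by participant or by record.
- **Further sensitivity analyses:** multiple imputation that respects the clusters, and a delta-adjusted (not-missing-at-random) analysis. The latter is needed because the primary model does not remove bias from unpredicted differences in people lost before week 12.

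The cost is wording and modest extra programming. Recruitment, sample size and participant burden do not change.

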**Methods:**

This cluster-randomized hybrid type 2 effectiveness-implementation trial will be conducted in 20 IDP camps or host communities in Maiduguri, Nigeria. Sites will be randomly assigned to receive a 12-week LSE program delivered either through in-person peer support groups or WhatsApp-facilitated mobile groups. The study will recruit 500 participants aged 13 years and older. Intervention effectiveness outcomes include the primary outcome of change in post-traumatic stress disorder (PTSD) symptoms assessed using the PCL-5 scale, and secondary outcomes of depression, anxiety, well-being, and life skills acquisition. Implementation outcomes will be assessed using the Acceptability of Intervention Measure (AIM), Intervention Appropriateness Measure (IAM), and Feasibility of Intervention Measure (FIM). Both sets of outcomes will be compared between the in-person and mobile delivery groups. Quantitative data will be analyzed using mixed-effects linear regression models, while qualitative data will be examined through reflexive thematic analysis. The study will be guided by the Reach-Effectiveness-Adoption-Implementation-Maintenance (RE-AIM) framework.

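### Propensity score matching is planned to correct the reported effect sizes for unmeasured confounders, which it cannot do, and its standing beside the intention-to-treat mixed model is not stated

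*Protocol article*

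**What the plan says.** All the analysis statements are in the Data analysis section of the protocol article.

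- Main analysis: "Quantitative data analysis will follow an intention-to-treat approach, using mixed-effects linear regression models to assess intervention effects on primary and secondary outcomes".
- Model terms: "Models will include fixed effects for time, group assignment, and their interaction, and random effects for clusters and participants".
- Measured confounding: "Baseline characteristics will be included as covariates to adjust for potential confounding".
- Reported effect measure: "Effect sizes will be expressed using Cohen’s (standardized mean differences) with 95% confidence intervals".
- Immediately after that: "To account for potential biases from unmeasured confounders, propensity score matching will be employed to adjust the effect size estimates".
- Separately, and without mention of matching: "Sensitivity analyses will be conducted to assess the robustness of the findings to different assumptions and methods".

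Allocation is by site. The abstract states: "Sites will be randomly assigned to receive a 12-week LSE program delivered either through in-person peer support groups or WhatsApp-facilitated mobile groups". The sample size section gives 10 clusters per arm.

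**The concern.** The matching sentence states a method and a purpose, and the method cannot deliver the purpose. A propensity score is the probability of being in one arm given the measured covariates. Matching on it balances those covariates. It does nothing for a variable that was not recorded, except for any part of it that the recorded variables predict.

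The second difficulty is the role of the matched result. The sentence follows directly on the definition of the reported effect measure and says that matching adjusts those estimates. It is not called secondary or a sensitivity analysis. A reader could be given a Cohen's d from a matched set and a test from the intention-to-treat model, with nothing to say which governs if they differ.

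This matters more here than in an individually randomised trial. The Study setting and participants section describes purposive recruitment linked to the delivery approach, and a phone-access criterion for the mobile arm only. Participants in the two arms could therefore differ in unrecorded ways even though sites are randomised. The plan would tell readers that this risk had been dealt with when it had not.

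**Working it through.** **1. What matching can balance.** Let X be the measured covariates, U an unmeasured one, and e(X) = P(arm = 1 | X). Among participants with the same e(X), the distribution of X is the same in both arms. Nothing follows for the part of U that is unrelated to X, because e(X) is computed without U. This holds for any caliper, ratio or algorithm, so details in an unseen SAP could not repair the stated purpose.

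**2. The plan's own figures, used only to set the dimensions of the check.** The sample size section gives d = 0.4, two-sided alpha 0.05, 80% power, ICC 0.05, 25 per cluster and 15% inflation.

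- Unclustered n = 99 per arm.
- Design effect = 1 + (25 − 1) × 0.05 = 2.2, so 99 × 2.2 = 217.8 per arm.
- Inflation by 15%: 217.8 × 1.15 gives 251 per arm (502 in total); 217.8 / 0.85 gives 257 per arm (514 in total).

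The stated 250 per arm and 500 in total agree within 3%. No figure in the plan is in dispute on this point.

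**3. Simulation.** There were 20 clusters of 25, ICC 0.05, true d = 0.40, and 600 runs per scenario. X and U were independent of each other, each with outcome coefficient 0.4. Matching was 1:1 nearest neighbour on the logit of the propensity score, with a caliper of 0.2 SD. Covariate adjustment was ordinary regression on arm and X, standing in for the fixed part of the mixed model. The imbalances, coefficients and matching algorithm are assumptions, not figures from the protocol.

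| Imbalance between arms | Unadjusted | Covariate regression | Matching | Share kept by matching |
|---|---|---|---|---|
| None | 0.411 | 0.411 | 0.409 | 90.2% |
| U only, 0.3 SD | 0.527 | 0.526 | 0.526 | 90.1% |
| X only, 0.3 SD | 0.526 | 0.404 | 0.406 | 85.3% |
| Both, 0.3 SD each | 0.632 | 0.512 | 0.511 | 85.5% |

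The bias expected from a 0.3 SD imbalance is 0.3 × 0.4 = 0.12, giving about 0.52. With U alone unbalanced, the bias is 0.527 − 0.40 = 0.127 before matching and 0.526 − 0.40 = 0.126 after it. With X alone unbalanced, matching leaves 0.406 − 0.40 = 0.006 and regression leaves 0.404 − 0.40 = 0.004. With both, each method removes the measured part and leaves the unmeasured part.

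The standard deviation of the estimates across runs was 0.12 to 0.14. The Monte Carlo error of each mean is therefore about 0.13 / √600 = 0.005, and differences in the third decimal carry no meaning.

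**4. Site-level factors.** Every participant in a site has the same arm and the same site characteristics, and there are only 10 sites per arm. Pairing similar individuals across arms leaves the sites themselves as they were allocated. Their balance rests on the randomisation of 20 units, and individual matching does not assure it.

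**The case against.** The best defence is that the mixed model remains the main analysis and matching is an extra. That is partly right, and it limits the point in several ways.

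- A reader might infer that matching replaces the intention-to-treat estimate. The text does not say so: assessment of intervention effects is assigned to the mixed model, and matching is said only to adjust the effect sizes. The surrounding sentences are also damaged in places, which is a reason not to read more into them. What stands is that the role of the matched figure is left open.
- A reader might infer that unmatched participants are necessarily lost, or that the cluster structure is broken. No algorithm is given. Full matching discards nobody, and a matched set can still be analysed with a cluster random effect. The 10–15% loss in the simulation belongs to its assumed caliper. A condensed article may leave such details to the SAP.
- A reader might infer a loss of power. Any figure would depend on an assumed match rate, and the model-based test need not be affected at all.
- A reader might call the analysis post hoc. It is stated in advance.

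It is also fair that adjustment has a real motive here, because recruitment and the phone criterion could unbalance the arms. But the model already adjusts for baseline characteristics, and in the simulated scenarios matching did no better. Where imbalance was absent or only measured, matching was redundant rather than harmful. None of this rescues the claim about unmeasured confounders.

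**Conclusion.** The sentence is wrong as written. Its stated purpose cannot be met, and that conclusion rests on the definition of a propensity score, not on the simulation. In the illustrative scenario, protection against an independent unmeasured imbalance was nil to within simulation error (0.526 against 0.527, truth 0.40). If U were correlated with X, matching would remove the part that X predicts, as would covariate adjustment.

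The consequence is an effect size of unstated standing. It may come from a different set of participants than the intention-to-treat model, and it carries a claim of protection that it does not have. The documents do not support a stronger conclusion: the intention-to-treat model stays in the plan, and neither a loss of participants nor a loss of power can be read from the text.

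**What to change.** Delete the matching sentence. In its place, state that each standardised effect is the adjusted between-arm difference from the intention-to-treat mixed model (at 12 weeks for the primary outcome) divided by a named SD, with a 95% CI that accounts for clustering. The pooled baseline SD is one reasonable choice among several; what matters is that one is fixed in advance. List the baseline covariates beforehand and include baseline PCL-5. It should enter once, either as a covariate or as the baseline visit among the repeated outcomes.

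If the investigators wish to keep matching, they should:

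- label it a sensitivity analysis for measured covariates only;
- keep the cluster random effect in the analysis of the matched set;
- remove the claim about unmeasured confounders.

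The cost is a change of wording and, at most, one planned analysis dropped or relabelled. The sample size of 500 and the data collection are unaffected.

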**Fig. 2 Fig2:**
[figure not shown]
The life skills education scope

In the in-person arm, participants will attend weekly 120-minute peer support group sessions facilitated by trained IDP men and women and supervised by local mental health workers. The groups will be gender- and age-segregated (13–15, 16–19, and 18 + years) to create safe spaces for open discussion and skills practice. Sessions will employ interactive and experiential learning techniques such as role-plays, storytelling, games, and art-based activities to enhance engagement and retention.

In the mobile arm (i.e. WhatsApp), participants will join gender- and age-specific mobile groups moderated by trained facilitators. The groups will receive weekly LSE content and exercises through a combination of messages, voice notes, images, and live audio sessions. Participants will be encouraged to share reflections, ask questions, and provide peer support through the WhatsApp chat. Facilitators will stimulate discussion, offer feedback, and monitor participant safety and engagement.

Both arms will receive the LSE intervention for a duration of 12 weeks, with an average of 10–12 participants per peer support group. Fidelity to the intervention will be assessed through structured observations, attendance records, and facilitator logs [52]. Participants will receive the equivalent of $20 US and be provided with snacks during the intervention. Participants will also have access to referral information for additional mental health and social services as needed.

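### If the stated cluster-and-participant model is reused for the gender-by-arm subgroup analysis, it leaves out the single-gender peer groups, and its interval is too narrow whenever outcomes correlate within those groups

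*Protocol article*

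**What the plan says.** In the Data analysis section of the protocol article, the mixed-effects linear models are specified as follows: "Models will include fixed effects for time, group assignment, and their interaction, and random effects for clusters and participants". Group assignment here means trial arm. The same section later adds that "Subgroup analyses will explore differential effects by gender, age, displacement duration, and baseline symptom severity". It writes out no separate model for these subgroup analyses.

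The section on the adapted intervention describes delivery. For the in-person arm: "The groups will be gender- and age-segregated (13–15, 16–19, and 18 + years) to create safe spaces". For the mobile arm, "participants will join gender- and age-specific mobile groups moderated by trained facilitators". Both arms run "with an average of 10–12 participants per peer support group".

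The sample size section gives 20 clusters, 10 per arm, averaging 25 participants, and an ICC of 0.05 for camps or communities. No ICC is given for peer groups, and no error rate or power is given for any subgroup test.

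**The concern.** The delivery design has three levels: participants within peer groups within clusters. The stated model has the first and the last. For most questions that may matter little, but gender is built into the missing level. Two groups in the same camp, one of men and one of women, differ in gender and also in membership, group dynamics and possibly facilitator. A model without a peer-group term treats the second kind of difference as independent variation between individuals, so it overstates how precisely a gender difference is known.

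Some group-level variation is plausible. Sessions rest on discussion, role-play and peer support, and the theory of change lists stronger social support and connectedness as a route to benefit.

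At stake is a finding that one delivery format suits men and the other suits women, when the difference came from how particular groups turned out. The Discussion says that results should inform the scale-up of delivery models, so such a finding could be read as guidance even though it is exploratory.

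**Working it through.** **The plan's own figure.** For d = 0.4, two-sided 5% and 80% power, n per arm = 2(1.96 + 0.84)²/0.4² = 98.1, rounded up to 99. The design effect is 1 + 24 × 0.05 = 2.2. Then 99 × 2.2 × 1.15 × 2 = 501, which reproduces the stated 500. This covers the overall arm comparison only, so there is no subgroup figure to reproduce.

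**Inputs from the article.** 20 clusters, 10 per arm, 25 per cluster, groups of 10–12. Groups per cluster: 25/12 to 25/10 = 2.1 to 2.5.

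**Assumptions.** One male and one female group in every cluster; m = 10 to 12.5 people per group; no true interaction; total variance 1, with a share r (the peer-group ICC) due to peer group within cluster. The article does not give r, so a range starting at zero is shown.

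**Why the cluster term does not help.** Write an outcome as cluster effect + group effect + individual effect. In the female-minus-male difference within a cluster, the cluster effect cancels. The true variance of that difference is (2/m)(σe² + mσg²), with σg² = r and σe² = 1 − r. Without a group term the model uses (2/m)s², where s² pools the between-group and within-group variation:

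s² = [18(σe² + mσg²) + 40(m − 1)σe²] / [18 + 40(m − 1)]

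Here 18 is 20 clusters less 2 arms, and 40(m − 1) is the within-group degrees of freedom. The variance is understated by the factor R = (σe² + mσg²)/s². The rejection rate is 2[1 − Φ(1.96/√R)], and the interval is too narrow by 1 − 1/√R.

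**Worked case, m = 11, r = 0.05.** σe² + mσg² = 0.95 + 0.55 = 1.50. s² = (18 × 1.50 + 400 × 0.95)/418 = 0.974. R = 1.54. Rejection rate = 2[1 − Φ(1.58)] = 11.4%.

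| Assumed peer-group ICC | R (m = 10 to 12.5) | Rejection rate at nominal 5% | Interval too narrow by |
|---|---|---|---|
| 0 | 1.00 | 5.0% | 0% |
| 0.01 | 1.10–1.12 | 6.1–6.4% | 4–6% |
| 0.02 | 1.19–1.24 | 7.3–7.9% | 8–10% |
| 0.05 | 1.49–1.62 | 10.8–12.3% | 18–21% |
| 0.10 | 2.01–2.27 | 16.6–19.3% | 29–34% |

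**Simulation.** With 10,000 trials per setting, 11 or 12 per group and a cluster share of 0.03, rejection was 7.5–8.1%, 12.0% and 18–19% at r = 0.02, 0.05 and 0.10. A baseline and 12-week version (12 per group, residual change variance 1) gave 7.5–8.0%, 10.8–11.3% and 16.0–17.1%. Testing against between-group variation on 18 degrees of freedom gave 4.6–5.4% at every r from 0 to 0.10.

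**Negative control.** A factor balanced within peer groups showed no material inflation (4.1–5.4% at r = 0.02 to 0.10). The alignment of gender with peer group is therefore what drives the result.

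**Overall arm comparison.** Arms differ between clusters, and each peer group lies inside one cluster. Group variance therefore shows up as between-cluster variance, and the cluster term carries it, provided that term acts on the change being compared.

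**Age.** Three bands by two genders make six strata. Filling all six with groups of 10–12 would need 60–72 people per cluster, against 25. Age bands may therefore differ mainly between clusters, where the cluster term does the work. The setting and participants section also conflicts on age: the target population is 13 and older, while the inclusion criterion is 18 or older. If only adults enrol, age would vary largely within groups, as in the negative control.

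**The case against.** The strongest reply is that the article does not say which model the subgroup analyses will use. The random effects are stated for the effects on primary and secondary outcomes, the subgroup sentence comes later, and detail of that kind often sits in an analysis plan. This stands in part: reuse of the main model is an inference. But the article does fix a random-effects structure, and that structure does not match its delivery design. An analysis plan that followed it would carry the gap forward.

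The second reply is that the analyses are exploratory, with no decision rule attached. That also stands, and it limits how serious the point is.

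The third is that everything depends on an ICC that the article does not report. At zero there is no inflation, and at 0.01 it is slight. The top of the range, 0.10, is twice the only ICC stated, which refers to camps or communities.

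A reader might go further in four ways that the article does not support. One is to quote a false-positive rate of 7–17% as fact; it is conditional on an assumed peer-group ICC. Another is to treat age like gender; two groups per cluster and the 13+/18+ conflict leave that open. A third is to extend the problem to the overall arm comparison. The last is to assume that attendance records already identify the peer group; the article says only that such records are kept.

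**Conclusion.** The point holds for the gender-by-arm analysis, conditionally. If the only stated model is used, and if outcomes correlate at all within peer groups, the interval is too narrow. With 20 clusters and one group of each gender per cluster, the size runs from nothing at a peer-group ICC of zero to a false-positive rate of about 16–19% at 0.10. Which value applies cannot be settled from the article. If some clusters hold groups of one gender only, part of the gender contrast moves between clusters and the inflation falls.

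For age, the point applies only where different age bands meet within a cluster, which cannot be judged until the eligibility statements are reconciled. The primary conclusion of the trial is not called into question. This is a worthwhile correction to an exploratory analysis.

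**What to change.** In the gender subgroup model, add a random effect for peer-support group nested in cluster, acting on the change from baseline. Test the interaction with small-sample degrees of freedom based on groups (18 if each cluster has one group per gender). Do the same for age if age bands differ within clusters, once the 13+ and 18+ statements have been reconciled. Record a peer-group ID for each participant during delivery and carry it into the outcome dataset, since it may be hard to recover later.

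The cost is one line of analysis text, one extra variable and somewhat wider subgroup intervals. Even with no group variance, testing on 18 degrees of freedom widens the interval by about 7% (2.101/1.96). Sample size and the primary analysis do not change.
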